### 2.8 Recruitment

Participants will be recruited to the CEHC from general practices, primary health network, other health professional or health organisations (e.g., aged care, hospital, residential aged care). Participants can self-refer. In addition, the study will be advertised broadly to the community and general practitioners (GPs), using brochures, media and newspaper stories and advertisements, and through Beyond Blue’s professional networks. The GPs in the local area will be informed about the study and provided with a brochure about how to improve detection and screening of anxiety and depression in their older patients.

Following referral, older adults will be screened over the telephone. Intake officers will assess likely suitability for the trial based on the inclusion and exclusion criteria outlined in Section 2.4. Older adults who are likely to meet the inclusion criteria will be sent participant information and consent forms. Intake officers will follow up to review understanding of the participant information and consent forms and to answer any questions. Older adults who are interested in participating will be asked to provide written informed consent, followed by completing full baseline measures according to the study design, including the ADIS administered by clinical psychologists, psychologists, or provisional psychologists at the Macquarie University CEHC. All participants will be allocated a deidentified alpha-numeric code by the research team. If a participant is deemed eligible after completion of the baseline assessment, they will be randomly allocated to one of the two treatment conditions by the research team (see Section 2.9 Assignment of intervention), and an appointment will be scheduled for the first treatment session. The average time between randomisation and entry into therapy is estimated to be two to four weeks depending on participant flow and clinician availability. If an older adult is ineligible for enrolment in the current study, the primary reason of ineligibility will be documented. Participants who do not consent or do not meet eligibility criteria will be offered alternative services at the CEHC as appropriate and/or referred to alternative services in the local area and/or to their GP.

### 2.9 Assignment of intervention

Eligible participants will be randomly allocated to receive enhanced CBT or standard CBT in a 1:1 ratio. The randomisation schedule will be generated using a computerised randomiser (www.randomizer.org) and placed into consecutively numbered sealed envelopes by an independent statistician. Block randomisation will be used to ensure that the two comparison groups are the same size.

### 2.10 Data collection methods

The clinician involved in the treatment of the participant will administer all the clinician-based instruments during treatment. Self-report measures are collected online, via pen-and-paper or over the telephone, at the participant’s choice. The semi-structured diagnostic interview (ADIS-5) will be administered at baseline, post-treatment, and at 12-month follow-up by independent assessors who are blind to treatment allocation. All participant data will be labelled using a deidentified alpha numeric code to ensure confidentiality.

All randomised participants will be followed up for data collection purposes at each time point three times using multiple formats (telephone messages, email and mail). If a participant misses an assessment time point, or if the intervention deviates from the protocol, participants will remain in the study and will be followed up for any subsequent assessments. Data collection will be discontinued for participants who formally withdraw their consent to participate, or who otherwise experience changes in their lives that preclude or complicate further participation; however, all data collected will remain in the study and be included in the analyses. Wherever possible, information about their decision to withdraw from the study will be collected to comply with CONSORT recommendations and facilitate correct reporting of adverse events.

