The primary outcome is the mean changes in Clinical Severity Rating (CSR) across all anxiety and depressive disorders on the ADIS-5 [24] at post-treatment. The ADIS -5 is a semi-structured interview for diagnosing psychiatric conditions according to DSM -5 [23] criteria. The CSR provides an overall severity rating comprising the level of distress and impairment associated with each DSM disorder from 0 (none) to 8 (very severe). A CSR of 4 or higher indicates that the disorder meets or exceeds the threshold for a formal DSM-5 diagnosis. The mean severity rating is calculated to examine overall changes in diagnostic severity over time. This interview will be administered by blinded clinical psychologists, psychologists, or provisional psychologists who will be trained in the interview administration and receive regular supervision to assist with diagnostic decisions.

Secondary outcomes will be measured by:

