### 2.12 Statistical methods

Data will be analysed using intention-to-treat principles. All participants will be included in analyses based on the condition to which they were initially allocated. Multiple imputation will be used to manage missing data. The efficacy of the programs will be established using mixed model analysis to compare the mean differences in clinical diagnostic severity (established by clinicians who are blind to treatment allocation) and scores on self-report measures at pre-treatment, post-treatment, and at a 12-month follow-up period.

Analysis will be a mixed model with random subject effect, fixed effects relating to group allocation (between-group), time (within-subject) and covariates. Interaction contrasts will be used if the time x group interaction reaches statistical significance, but the main effect contrast will be used if not.

Statistical inference will be based on the nonparametric bootstrap if the assumption of Normality is violated. The same process will be used for the secondary hypotheses to compare the groups on all outcome measures. Differences between groups in baseline characteristics, and therapy factors (e.g., sessions attended, therapist alliance) will be examined and controlled for in analyses.

In addition, an economic evaluation will be undertaken to measure the relative benefit in health outcomes and resource use for the enhanced intervention compared to standard CBT. Moderation analyses will examine the impact of moderators on treatment outcomes.

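### Data collection ends when life changes merely complicate participation, even without withdrawn consent, which can create avoidable missing outcomes

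*Protocol article*

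**What the plan says.** Section 2.10 (Data collection methods) starts from broad follow-up: "All randomised participants will be followed up for data collection purposes at each time point three times using multiple formats". For a missed assessment or a deviation from the intervention, it adds that "participants will remain in the study and will be followed up for any subsequent assessments".

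It then names who is no longer followed. "Data collection will be discontinued for participants who formally withdraw their consent to participate", and the sentence continues with a second group: "or who otherwise experience changes in their lives that preclude or complicate further participation". Data already collected are kept and analysed, and reasons for leaving are sought where possible.

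The same section offers low-burden modes for part of the battery: "Self-report measures are collected online, via pen-and-paper or over the telephone, at the participant’s choice". It states no mode for the diagnostic interview that yields the primary outcome.

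Section 2.6 defines that outcome: "The primary outcome is the mean changes in Clinical Severity Rating (CSR) across all anxiety and depressive disorders on the ADIS-5 [24] at post-treatment". Section 2.12 says of the analysis that "All participants will be included in analyses based on the condition to which they were initially allocated" and, on missing values, only that "Multiple imputation will be used to manage missing data".

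**The concern.** The second ground for ending data collection contains two different situations. When a life change precludes participation, the data cannot be had. When it only complicates participation, the person may still consent and still be reachable. The protocol treats the two alike: it sets no threshold for complication, names nobody who decides, and does not require that the participant be offered a reduced assessment or decline one.

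Participants are 65 or older with an anxiety or depressive disorder. Illness, bereavement, a move or a new caring role could plausibly affect diagnostic severity, loneliness, social network and participation, which are the trial's outcomes. If the change comes after the last observed value, its effect on the outcome is unseen.

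Two things are at stake. One is precision, because each lost post-treatment rating reduces the information behind the primary comparison. The other is possible bias in the arm contrast if the loss, or the outcome shift among those lost, differs between arms.

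**Working it through.** **1. The rules side by side.** Take a participant who misses the post-treatment visit because of a family illness, has not withdrawn consent, and could be reached by telephone. Under the missed-assessment rule in section 2.10 this person stays due for later assessments. Under the life-change rule in the same section data collection ends. Both descriptions fit, and nothing in the text says which prevails.

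**2. The planned sample size.** Inputs from section 2.7: d = 0.5, power 90%, two-sided alpha 0.05, 86 per arm.
- Normal approximation: n per arm = 2(1.960 + 1.282)² / 0.5² = 2 × 10.51 / 0.25 = 84.1, rounded up to 85.
- Two-sample t-test: 85.03, rounded up to 86 per arm, or 172 in total. This matches the protocol. Power at 86 per arm is 90.3%.

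**3. Whether there is a reserve for loss.** The 15% in section 2.7 covers people found unsuitable at the baseline assessment, before randomisation (172 / 0.85 = 202.4, against at least 200 to be recruited). The 172 therefore assumes that every randomised participant supplies the outcome.

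**4. Precision.** The protocol gives no dropout rate, so the loss is an assumed range. Observed n per arm = 86 × (1 − loss); two-sample t-test on observed cases, unadjusted:

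| Total loss | n per arm | Power |
|---|---|---|
| 0% | 86 | 90.3% |
| 5% | 81.7 | 88.8% |
| 10% | 77.4 | 87.1% |
| 15% | 73.1 | 85.1% |
| 20% | 68.8 | 82.9% |

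These are total losses from all causes. Only the part due to mere complication can be recovered. If, as an assumption, that were half of a 10% loss, removing it would move power from 87.1% to 88.8%.

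**5. Bias in the arm contrast.** Let f be the fraction missing in an arm and k the number of SDs by which the missing outcomes are worse than their imputed values. Then bias = f₁k₁ − f₀k₀. With k equal in both arms:
- 10% against 5%, k = 1: (0.10 − 0.05) × 1 = 0.05 SD, which is 10% of the planned 0.5.
- 15% against 5%, k = 1: 0.10 SD, or 20% of 0.5.
- 10% against 5%, k = 0.5: 0.025 SD.
- Equal fractions and equal k: 0.

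**6. Check by simulation.** Large samples, true effect −0.50 SD (lower is better), assumed baseline-outcome correlation 0.5, regression imputation on baseline within arm:

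| Missing, enhanced / standard | Missingness depends on | Estimate |
|---|---|---|
| 20% / 10% | baseline | −0.502 |
| 15% / 15% | outcome | −0.500 |
| 20% / 10% | outcome | −0.555 |
| 10% / 20% | outcome | −0.444 |

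Imputation recovers the effect when the driver of loss is observed, and when outcome-driven loss is balanced between arms. With unbalanced outcome-driven loss it misses by about 0.055 SD, in either direction.

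**The case against.** The strongest reply is that the clause describes people who drop out without formal paperwork. The sentence after it speaks of participants deciding to leave the study, so participant choice may be what was meant. On that reading little of the loss is avoidable. The reading is possible, but the clause does not say it. If it is what was intended, removing complication as a ground costs nothing.

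It can also be said that a general rule followed by exceptions is no contradiction. That is fair as logic, and is why the point is that the passages sit badly together. The exception is so loosely drawn that it can absorb cases the general rule was written to keep.

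Several stronger readings are tempting, and the documents do not support them.
- A reader might infer that therapists who know the arm choose whom to stop. Section 2.10 gives no one that decision.
- A reader might infer that those doing worst are removed selectively. A link between life changes and outcome is plausible but undocumented, and a relocation need not imply greater severity.
- A reader might infer a breach of intention to treat. Section 2.12 uses the term for analysis by allocated arm, and section 2.10 keeps the data already collected.
- A reader might infer that the imputation assumes data missing at random with no sensitivity analysis. The protocol names only the method; the rest commonly belongs in a statistical analysis plan, which is not shown.

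Nor do the documents suggest that loss will differ by arm. Both arms receive 12 weekly one-hour individual sessions from therapists who deliver both treatments.

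**Conclusion.** The point holds as a weakness in the data-collection rule. As written, section 2.10 permits data collection to end for people who still consent and may be reachable, and this can create avoidable gaps at post-treatment and 12 months.

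The size cannot be fixed from the documents. On assumed figures, a 10% total loss takes power from about 90% to 87%, and only the complication share of that loss can be recovered. The contrast bias of 0.05 SD rests on 10% against 5% stopped and on a 1 SD shift beyond what imputation captures, which is a severe assumption. With equal fractions and equal shifts there is no bias in the contrast, and the cost is precision alone. The change is worth making because it is cheap and because later analysis cannot restore uncollected outcomes.

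**What to change.** In section 2.10, delete complication as a ground. Stop data collection only when a participant withdraws consent to, or declines, further data collection, or when collection is impossible. State that participants whose circumstances are merely complicated remain due for the post-treatment and 12-month assessments, with the blinded ADIS-5 severity rating offered by telephone as the minimum set. Report the number of participants whose data collection was stopped, with reasons, by arm, including any already stopped under the present wording.

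The cost is a small amendment to the protocol, and to the consent wording where it repeats the rule, plus some extra contact effort. Participants may still decline any assessment, so the change reduces missing data without eliminating it.

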### 2.11 Data management and confidentiality

To safeguard the confidentiality of the participants and to ensure proper handling of all data, processing of all data reporting complies with CONSORT recommendations and is in accordance with the National Statement on Ethical Conduct in Human Research [38]. Participants will provide electronic or written informed consent. All participant data will be allocated a deidentified code so that confidentiality is maintained during the study, and when the data are stored. Deidentified data will be stored in password protected secure online data storage repositories indefinitely at Macquarie University. Only chief investigators, the independent biostatistician, the project manager, and research assistant will have access to this deidentified data in order to facilitate assessment and welfare of participants in a crisis (telephone number, email address). This information is stored in a separate password protected file on the Macquarie University server. Linked resource utilisation data will be extracted by the NSW Centre for Health Record Linkage (CHeReL) and the Commonwealth Department of Human Services, using the personal identifiers of consenting study participants. The content data from the routine data collections will be returned to the research team in a deidentified format, so that it can be merged with trial data using the study specific IDs. This is in line with the ‘separation principle’ that ensures the maintenance of distinct and disjointed research datasets that mitigate re-identification risks.

### 2.12 Statistical methods

Data will be analysed using intention-to-treat principles. All participants will be included in analyses based on the condition to which they were initially allocated. Multiple imputation will be used to manage missing data. The efficacy of the programs will be established using mixed model analysis to compare the mean differences in clinical diagnostic severity (established by clinicians who are blind to treatment allocation) and scores on self-report measures at pre-treatment, post-treatment, and at a 12-month follow-up period.

Analysis will be a mixed model with random subject effect, fixed effects relating to group allocation (between-group), time (within-subject) and covariates. Interaction contrasts will be used if the time x group interaction reaches statistical significance, but the main effect contrast will be used if not.

Statistical inference will be based on the nonparametric bootstrap if the assumption of Normality is violated. The same process will be used for the secondary hypotheses to compare the groups on all outcome measures. Differences between groups in baseline characteristics, and therapy factors (e.g., sessions attended, therapist alliance) will be examined and controlled for in analyses.

In addition, an economic evaluation will be undertaken to measure the relative benefit in health outcomes and resource use for the enhanced intervention compared to standard CBT. Moderation analyses will examine the impact of moderators on treatment outcomes.

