### 2.4 Eligibility criteria

Eligible participants are adults aged 65 years or older with a primary diagnosis of an anxiety and/or unipolar depressive disorder according to the Diagnostic and Statistical Manual of Mental Disorders– 5^th^ Edition (DSM-5) [23] criteria assessed by the Anxiety Disorders Interview Schedule for DSM-5 (ADIS-5) [24]. In addition, participants will need to have adequate understanding of the English language as indicated by the ability to read a local newspaper.

Individuals will be excluded if they have current psychotic or bipolar traits, active suicidal intent, significant uncorrected hearing loss and likely moderate to severe dementia as screened by the six-item Cognitive Impairment Screener [25]. Participants currently using psychotropic medications (e.g., anxiolytic and antidepressant medication) will not be excluded, but participants will need to be stabilised on medications for one month before baseline assessment. Participants will report medication type, dosage and frequency of use, and whether the medications were prescribed for management of depression or anxiety. All medication changes will be noted at each assessment and those related to anxiety and mood management will be statistically controlled in analyses.

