### 2.7 Sample size

Based on review of the available literature and our pilot study results comparing this enhanced CBT program to an active control group, we predict the enhanced CBT program to produce a controlled effect size (against standard intervention) of Cohen’s *d* = 0.5. Therefore, based on a moderate effect of Cohen’s *d* = 0.5, with power at 90% and, alpha at 0.05 (two-sided), 172 participants (86 equally randomised to each condition) in total are required, with the expectation that 15% of participants will be unsuitable based on outcomes of the baseline assessment (based on previous studies in our clinic that use a brief intake screener to determine likely eligibility into the program prior to baseline assessment), at least 200 participants will be recruited. In order to understand the representativeness of the population, demographic information will be collected with respect to sex, age, country of birth, ethnicity, education, marital status, income, employment status, living circumstances (e.g., retirement villages), pre-existing health conditions, psychiatric history (including duration), and current medications (type, dosage, and frequency) at time of intake/baseline assessment, post-treatment, and at each follow-up assessment.

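### The primary mixed model leaves the pre-randomisation baseline severity rating free by arm, so the post-treatment contrast is unbiased but less precise than a baseline-constrained one

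*Protocol article*

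**What the plan says.** The primary outcome (section 2.6) is defined thus: "The primary outcome is the mean changes in Clinical Severity Rating (CSR) across all anxiety and depressive disorders on the ADIS-5", taken at post-treatment. The same section has the baseline assessment (T1) done before randomisation, T2 at 14 weeks and T3 at 12 months.

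Section 2.12 gives the model: "Analysis will be a mixed model with random subject effect, fixed effects relating to group allocation (between-group), time (within-subject) and covariates". It lists pre-treatment, post-treatment and 12-month scores as the quantities compared. It uses interaction contrasts when the time-by-group term is significant and the group main effect when it is not.

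The covariates named are baseline characteristics and therapy factors that differ between groups (2.12) and medication changes (2.4). Baseline CSR is not among them by name. No residual covariance structure is given.

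Section 2.7 assumes a standardised difference d of 0.5 and concludes: "with power at 90% and, alpha at 0.05 (two-sided), 172 participants (86 equally randomised to each condition) in total are required". It does not say which SD scales d.

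**The concern.** Because baseline precedes randomisation, the two arms have the same expected CSR at T1. A model that estimates a separate baseline mean in each arm does not use that fact. With complete data, its T2 interaction contrast is the difference between arms in the mean of T2 minus T1. The chance baseline difference is subtracted in full, whether or not baseline predicts T2 that strongly. A model that uses the common baseline subtracts only the part that baseline predicts. What is at stake is the precision of the primary comparison.

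A second, lesser matter is the covariance. The natural reading of a random subject effect with nothing added is one variance and one correlation across all three visits. Equal variances may fail here. Entry requires a disorder ("Eligible participants are adults aged 65 years or older with a primary diagnosis of an anxiety and/or unipolar depressive disorder"), and "A CSR of 4 or higher indicates that the disorder meets or exceeds the threshold for a formal DSM-5 diagnosis", so ratings at entry may be less spread out than later ratings, which can fall to 0.

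**Working it through.** **Inputs from the document.** Two-sided alpha 0.05, power 90%, d = 0.5, 86 per arm, 1:1 allocation, baseline before randomisation. **Assumed**, because the document gives no value: the correlations between visits (r12, r13, r23 for T1–T2, T1–T3, T2–T3) and the ratio s of baseline SD to T2 SD. Complete data and large-sample formulas are used. Imputation and further covariates are not modelled.

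**The plan's own figure.** A two-sample t-test with d = 0.5 has power 0.8999 at 85 per arm and 0.9032 at 86. The stated 172 reproduces.

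**Precision of the T2 contrast.** Take the T2 variance as 1 and write r for r12. Apart from the common factor 2/86:

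- free baseline (difference in change): s² + 1 − 2rs
- common baseline, unstructured covariance: 1 − r²

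The first minus the second is (s − r)², which is never negative. The constrained contrast is therefore never less precise, and the two are equal only when s = r.

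With equal SDs (s = 1) the factors are 2(1 − r) and 1 − r², so their ratio is (1 + r)/2:

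| r | free | constrained | ratio | variance cut |
|---|---|---|---|---|
| 0.3 | 1.40 | 0.91 | 0.65 | 35% |
| 0.4 | 1.20 | 0.84 | 0.70 | 30% |
| 0.5 | 1.00 | 0.75 | 0.75 | 25% |
| 0.6 | 0.80 | 0.64 | 0.80 | 20% |
| 0.7 | 0.60 | 0.51 | 0.85 | 15% |

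With a smaller baseline SD:

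| s | r | free | constrained | ratio | variance cut |
|---|---|---|---|---|---|
| 0.6 | 0.3 | 1.00 | 0.91 | 0.91 | 9% |
| 0.6 | 0.5 | 0.76 | 0.75 | 0.99 | 1% |
| 0.8 | 0.3 | 1.16 | 0.91 | 0.78 | 22% |
| 0.8 | 0.5 | 0.84 | 0.75 | 0.89 | 11% |

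**Standard error under a random intercept with independent residuals.** This model estimates one within-subject variance: the average of the three variances minus the average of the three covariances. It gives the T2–T1 contrast twice that value. With equal SDs the modelled factor is 2[1 − (r12 + r13 + r23)/3], against a true factor of 2(1 − r12). The standard error is therefore too small exactly when r13 + r23 > 2·r12, and too large when the inequality is reversed. The type I error is 2[1 − Φ(1.96·√(modelled/true))]:

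| SDs (T1/T2/T3) | r12/r13/r23 | modelled | true | type I error |
|---|---|---|---|---|
| 1/1/1 | 0.5/0.5/0.5 | 1.00 | 1.00 | 5.0% |
| 1/1/1 | 0.5/0.4/0.6 | 1.00 | 1.00 | 5.0% |
| 1/1/1 | 0.4/0.3/0.7 | 1.07 | 1.20 | 6.5% |
| 1/1/1 | 0.3/0.25/0.6 | 1.23 | 1.40 | 6.6% |
| 1/1/1 | 0.6/0.4/0.5 | 1.00 | 0.80 | 2.8% |
| 0.7/1/1 | 0.3/0.25/0.6 | 1.00 | 1.07 | 5.8% |
| 0.7/1/1 | 0.5/0.4/0.6 | 0.84 | 0.79 | 4.3% |

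The error goes both ways and is modest in these cases.

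**The case against.** **This is a preference about efficiency, and an article may leave such detail to the SAP.** It stands that the planned interaction contrast is unbiased under randomisation, and that covariance structure and degrees of freedom may be set in a document not shown. But the article does state the model, the time points in it and the contrast, and that stated choice can be improved with data already collected. Baseline CSR might enter as a baseline characteristic found to differ between arms, but only after an observed imbalance and not as a fixed part of the primary analysis.

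**A reader might infer that the planned standard errors are wrong.** The document does not support that. It does not say that the random subject effect is the only source of correlation. Even if it is, a T2–T3 correlation above the T1–T2 correlation is not enough to make the standard error too small: at 0.5/0.4/0.6 it is exact. Nor are unequal variances certain. The threshold of 4 applies to a diagnosed disorder, while the outcome averages over all anxiety and depressive disorders, so it may have no floor at 4.

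**A reader might also infer that 86 per arm is too few.** With d in T2 SD units and equal SDs, the planned contrast has 79.1% power at r = 0.3 and 84.9% at r = 0.4, against 93.0% and 94.7% with the constraint (normal approximation). But the condition for keeping the nominal power is s² + 1 − 2rs ≤ 1, that is r ≥ s/2. It is r ≥ 0.5 only when s = 1. At s = 0.6 and r = 0.3 the free factor is 1.00 and the power is the planned one. The primary outcome is a change, and if d is scaled by the SD of change, 86 per arm gives 90.3% as planned.

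**The figures apply only when the interaction contrast is used.** That is true. The fallback to a group main effect is a separate question and adds no weight here.

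**Conclusion.** The point holds as an improvement in precision, not as an error in the plan. Modelling a pre-randomisation baseline as a free outcome level makes the T2 contrast a change-score comparison. Using the common baseline lowers its variance by 15–35% for r of 0.3–0.7 with equal SDs, or by about 1–22% with s of 0.6–0.8 and r of 0.3–0.5. The true gain could be close to nothing if s is near r. All these ranges rest on assumed correlations and SDs and on complete data.

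The covariance is a supporting matter. Under a random intercept with independent residuals, the type I error for the T2 contrast ran from about 2.8% to 6.6% in the assumed cases. Neither a faulty standard error nor a faulty sample size is established.

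**What to change.** State the primary estimate as the difference between arms in mean CSR at T2, from a constrained longitudinal model: T1, T2 and T3 as outcomes, one baseline mean common to both arms, and arm-by-time terms at T2 and T3. An alternative that estimates the same T2 difference takes T2 and T3 as outcomes with baseline CSR, interacting with time, as a covariate. With a common baseline, the arm difference at T2 is also the arm difference in mean change, so the stated primary outcome is kept.

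Use an unstructured 3×3 covariance with Kenward–Roger degrees of freedom. It lets the model use the actual T1–T2 relation and guards the standard error against unequal variances or correlations. If the SAP already specifies this, a sentence in section 2.12 is enough.

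The cost is wording and a few covariance parameters: six for the unstructured matrix, against two for a random intercept with independent residuals. No new data are needed, and 172 participants need not change.
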